### Withdrawal and discontinuation

2.18

Participants are withdrawn from the study if they are newly diagnosed with a serious disease or if they miss one or more assessments, or if they withdraw their informed consent

If a participant withdraws from the study or discontinues the trial, we won't replace them.

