### Primary and secondary outcomes

2.8

The primary endpoint of this trial is the change in BFA of participants enrolled in this randomized controlled study, calculated at baseline and after the 12-week intervention period. To evaluate BFA, the study staff will conduct a BFS assessment for each participant, comprising 45 different noninvasive tests performed at University Clinic of Obstetrics and Gynecology, Inselspital Bern.

The secondary endpoint includes the assessment of changes in climacteric symptoms, particularly hot flushes, and alterations in hsCRP levels and oxidative stress. These parameters will be measured concurrently with the BFS assessments for each participant. Variations in participant adherence and engagement may influence both the primary and secondary end points, for example due to lack of motivation or limited time availability. Furthermore, potential imbalances in the frequency or quality of home-based yoga sessions could affect the significance of the study outcomes.

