### Sample size and power calculation

2.11

We will include a maximum of 72 postmenopausal women experiencing at least four hot flushes per day. The study staff randomly assign participants to one of this two groups: an intervention group comprising up to 36 participants receiving the Iyengar Yoga classes, and a control group comprising up to 36 postmenopausal women who will not receive any intervention. The sample size of 36 participants per group is sufficient to detect a difference with an effect size of 0.75 at a significance level of 5% (two-tailed) and a statistical power of 80%, as calculated using the nonparametric Mann–Whitney *U*-test.

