### Statistical analysis

2.17

For the primary outcome, the BFA, we will use the nonparametric Mann–Whitney *U*-test. The 45 individual BFS tests will be evaluated exploratively as secondary variables.

To maintain consistency between the sample size calculation and the planned analysis, the significance level for the primary analysis will be set at 0.05 (two-sided), which aligns with the assumptions used to estimate the required sample size. Rejection of the null hypothesis would indicate that a weekly 12-week yoga intervention significantly reduces BFA in postmenopausal women. The sample size of 36 participants per group (intervention and control) provides 80% power to detect an effect size of 0.75 using a two-sided Mann–Whitney *U*-test.

The statistician will perform the data analysis using IBM SPSS software and will compare all groups with respect to outcome variables and covariates. The analysis will be performed according to the intention-to-treat principle.

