### Missing data and drop-outs

2.19

In cases of missing data, we will use the available data to calculate correlation coefficients; missing values will not be replaced. A dropout rate of up to 15% is considered acceptable to maintain statistical significance. Data collected up to dropout will be used for analysis.

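### The withdrawal and missing-data rules confine the primary test to completers by randomised arm, although the protocol declares intention-to-treat

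*Protocol article*

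**What the plan says.** All places are in the protocol article.

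- Section 2.17 (Statistical analysis): "The analysis will be performed according to the intention-to-treat principle". The test is fixed there too: "For the primary outcome, the BFA, we will use the nonparametric" Mann–Whitney U-test.
- Section 2.18 (Withdrawal and discontinuation): "Participants are withdrawn from the study if they are newly diagnosed with a serious disease or if they miss one or more assessments". Withdrawn consent is the third reason. The withdrawal is from the study, not only from yoga, and nobody is replaced.
- Section 2.19 (Missing data and drop-outs): "we will use the available data to calculate correlation coefficients; missing values will not be replaced". It adds "Data collected up to dropout will be used for analysis" and tolerates dropout of up to 15%.
- Section 2.8 (Primary and secondary outcomes): the endpoint is the change in BFA, "calculated at baseline and after the 12-week intervention period".
- Section 2.3 and Table 1: the biofunctional status (BFS), from which BFA is derived, is assessed twice, at the first visit and at the second visit in week 14.

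**The concern.** Intention-to-treat means that every randomised woman counts in her assigned arm. Sections 2.18 and 2.19 together do not allow that. They end follow-up for certain events after randomisation, bar replacement of the missing outcome, and name a test that needs the outcome.

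One of those events, a new serious disease, is plausibly related to an outcome that measures functional health. Removing such women makes the comparison depend on who stayed well, and randomisation no longer fully protects it. The trial is open-label and the arms differ in burden and contact. Yoga women have a weekly class and two home sessions (section 2.5) and receive weekly calls, while controls have no active monitoring (Discussion). Equal, random loss therefore cannot be taken for granted.

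This is not a detail that an analysis plan could settle later. An outcome that was never collected, because the protocol ended the woman's participation, cannot be recovered at the analysis stage.

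**Working it through.** **1. The plan's own figure.** Section 2.17 states: "The sample size of 36 participants per group (intervention and control) provides 80% power to detect an effect size of 0.75", two-sided 5%. I take 0.75 as a standardised mean difference. For normal data the Mann–Whitney test has relative efficiency 3/π = 0.955 (a general result, not from the protocol).

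- All 36 per arm analysed: effective n = 36 × 0.955 = 34.4. Noncentrality = 0.75 × √(34.4/2) = 3.11. Power = Φ(3.11 − 1.96) = 87.5%. The noncentral t gives 86.5% and 20,000 simulated trials give 86.4%.
- 15% lost: 36 × 0.85 = 30.6 per arm, effective n 29.2, noncentrality 2.87, power 81.8%. The noncentral t gives 80.5%; simulation with 31 per arm gives 80.8%.
- With the minimum efficiency of 0.864 instead, the noncentral t gives 82.9% for 36 and 76.3% for 30.6.

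So 36 per arm meets the stated 80%. For normal data it still does so with the tolerated loss. The sample size is not the problem.

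**2. Each kind of randomised woman, traced through the text.**

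| Woman | Section 2.18 | Change in BFA | In primary test |
|---|---|---|---|
| Attends both visits, whatever her yoga attendance | not withdrawn | available | yes, in assigned arm |
| New serious disease, could attend week 14 | withdrawn | not collected | no |
| Misses the second visit, would come late | withdrawn | not collected if withdrawal blocks the late visit | no |
| Never returns, or withdraws consent | withdrawn | missing under any rule | no |

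Rows 2 and 3 are where the rule itself loses outcomes. Row 4 would be missing anyway.

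**3. Whether section 2.19 repairs this.** With two assessments, what exists before dropout is a baseline value. It yields neither a change in BFA nor a week-14 BFA, so the named test cannot use it. The only stated missing-data method concerns correlation coefficients, which play no part in a two-group rank comparison.

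**4. Scale of loss.** At the tolerated limit, 0.15 × 72 = 10.8, about 11 women, leaving about 61 in the test.

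**5. Possible bias.** Let a fraction p of the yoga arm be missing, with outcomes δ worse than the yoga completers, and let control loss be random. The true arm mean is the completers' mean plus p × δ, so the bias is p × δ. The values of δ and the one-woman case are assumptions.

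| Case | p × δ | Share of 0.75 |
|---|---|---|
| One of 36 removed, 1 SD worse | 1/36 × 1 = 0.028 SD | 3.7% |
| 15% lost, 0.5 SD worse | 0.15 × 0.5 = 0.075 SD | 10% |
| 15% lost, 1 SD worse | 0.15 × 1 = 0.15 SD | 20% |

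**6. False-positive rate, as illustration.** I simulated 20,000 trials with no true effect, 5 of 36 yoga women lost and no control losses. The two-sided 5% test rejects in 6.2% of trials if loss correlates 0.3 with outcome (mean shift 0.076 SD) and in 7.7% at 0.5 (0.124 SD). If exactly the five worst outcomes vanish it rejects in 16.6% (0.249 SD), an extreme that nothing in the protocol suggests.

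**The case against.** The case for leaving the text alone has several good parts.

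- **Non-adherence does not trigger withdrawal.** A reader might infer that women who skip yoga are dropped, making this a per-protocol analysis. Section 2.18 does not say so. Such women stay in their arm if they attend both visits, so the usual hazard of a behavioural trial is absent. This stands.
- **No-shows lack an outcome under any rule.** This stands for women who never return. Section 2.6 also foresees a second examination for everyone, and section 2.7 provides reminder calls and individual results to limit loss. The missed-assessment clause therefore matters only where it would block a visit that could still happen.
- **Serious disease should be uncommon.** Section 2.3 screens for serious and chronic illness and the period is 12 weeks. The documents give no rate, so the effect may be near the lower end of the range. This stands.
- **The direction is open.** A reader might infer that the rule favours yoga by 10 to 20% of the design effect. That assumes selective yoga loss, random control loss, and the whole tolerated 15% charged to the rule. The weekly calls could equally retain yoga women and leave selective loss among controls. The documents do not settle this.
- **Modelling alone would not cure it.** A mixed model, or imputation from baseline BFA and age, assumes that loss is random given those variables. With one follow-up value it gives nearly the same answer as a baseline-adjusted analysis of completers. This stands, and it is why collecting the outcome comes first.

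None of this reconciles section 2.17 with sections 2.18 and 2.19, or justifies ending follow-up for a woman who is ill but willing to attend.

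**Conclusion.** The point holds. As written, the primary analysis covers completers in their randomised arms, not all randomised women, and the intention-to-treat statement in section 2.17 is not met. The serious-disease clause is the clearest fault. The missed-assessment clause is secondary, and the correlation-coefficient sentence is a misfit that does not itself cause bias.

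The documents fix neither the size nor the direction of bias. My range of about 0.03 to 0.15 SD rests on assumed outcome differences and, at the upper end, on the full 15% loss in the yoga arm with random control loss. That upper end includes women who would be missing under any rule. The documents do not support calling the trial underpowered or the analysis per-protocol.

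**What to change.** 1. In section 2.18, separate stopping yoga, a decision left to the investigator, from leaving follow-up. Let only withdrawal of consent end data collection.
2. Delete a missed assessment as a reason for withdrawal.
3. Seek the week-14 BFS, already in Table 1, from every consenting randomised woman, and analyse her in her assigned arm.
4. In section 2.19, replace the correlation-coefficient sentence with a rule for women who have no second BFA, compatible with the primary test. Add a sensitivity analysis for informative loss, for example imputing yoga-arm dropouts from the control arm.
5. If no such rule is wanted, describe the primary analysis in section 2.17 as available-case by randomised arm instead of intention-to-treat.

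The cost is protocol wording, a few more second visits within the existing schedule, and a little more analysis work.

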### Missing data and drop-outs

2.19

In cases of missing data, we will use the available data to calculate correlation coefficients; missing values will not be replaced. A dropout rate of up to 15% is considered acceptable to maintain statistical significance. Data collected up to dropout will be used for analysis.

### Adverse events

2.20

Both the Investigator and the Sponsor-Investigator assess the causality of each adverse event with respect to the trial intervention. Events assessed as possibly, probably, or definitely related are classified as related to the intervention, following the International Council for Harmonization E2A guidelines (20).

The Sponsor-Investigator assesses the severity of each adverse event as mild, moderate, or severe. If there is a severe adverse event related to the trial intervention, the Investigator reports the severe adverse event to the Ethics Committee via Business Administration System for Ethics Committees within 15 days.

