### Inclusion and exclusion criteria

2.3

Participants were eligible for this study if they provide written informed consent and were postmenopausal. Postmenopause is defined as either 12 months of spontaneous amenorrhea, six months of spontaneous amenorrhea with serum follicle stimulating hormone levels greater than 40 mIU/mL, or six weeks after a bilateral oophorectomy with or without hysterectomy. We included only postmenopausal women because the definition is clear, allowing for a more homogeneous study population. Eligible participants must experience at least four hot flushes per day, as assessed using the Menopause Rating Scale II questionnaire (16). They must not have practiced yoga regularly in the past two years. Participants must be good German speakers and willing to attend all 12 guided yoga classes as well as two 45-minute home-based yoga sessions per week. We included only German-speaking participants, as the BFS was developed in German and this ensures that there are no comprehension issues. In addition, they must agree to attend two BFS assessments and to provide blood samples.

Participants are excluded from the study if they have had an acute or serious disease within the past two years, such as cancer or major surgery, or if they have autoimmune or chronic inflammatory diseases, including rheumatism or thyroid dysfunction. Individuals with mental illnesses, such as depression or anxiety disorder, measured with the Hospital Anxiety and Depression Scale score (17), acute or chronic back pain, or herniated discs are also excluded. Additional exclusion criteria include current hormone replacement therapy, smoking more than 20 cigarettes per day or having a history of more than 20 pack-years, and alcohol consumption exceeding 30 g per day (equivalent to more than 1 L of beer or 0.3 L of wine). Individuals who have participated periodically in yoga classes within the last two years, those unable or contraindicated to undergo the intervention, or participants incapable of making informed judgments or under legal tutelage are also excluded.

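### As printed, the 15-day report to the Ethics Committee is triggered by the intensity grade of an adverse event, not by its seriousness

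*Protocol article*

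**What the plan says.** Section 2.20 of the protocol article sets out safety reporting in three steps.

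- **Relatedness.** "Events assessed as possibly, probably, or definitely related are classified as related to the intervention". The ICH E2A guideline is cited in this sentence.
- **Grading.** "The Sponsor-Investigator assesses the severity of each adverse event as mild, moderate, or severe".
- **Reporting.** "If there is a severe adverse event related to the trial intervention, the Investigator reports the severe adverse event to the Ethics Committee", and this is done "via Business Administration System for Ethics Committees within 15 days".

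The word serious appears in two other rules of the article, and neither concerns the classification of adverse events. Section 2.3 (Inclusion and exclusion criteria) uses it for medical history: "Participants are excluded from the study if they have had an acute or serious disease within the past two years". Section 2.18 (Withdrawal and discontinuation) uses it for new disease during the trial: "Participants are withdrawn from the study if they are newly diagnosed with a serious disease".

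**The concern.** Intensity and seriousness are different properties of an adverse event. Intensity says how strongly the event is felt or expressed. Seriousness says what it led to. The two often go together but need not. As an illustration of my own, not taken from the article: an injury during practice that leads to a hospital admission could be graded moderate, and a muscle ache without lasting consequence could be graded severe.

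A rule that sends reports to an ethics committee should catch events by their consequence for the participant. If it is tied to intensity, whether an event with a serious outcome is reported depends on a grade that was not designed to measure outcome. At stake is participant safety reporting, not the estimate of the yoga effect.

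**Working it through.** No power, rate or effect calculation applies, and the plan states no figure to reproduce. The check is a reading of the rule and a search for any other rule that would repair it.

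**Step 1: what the trigger word means.** The sentence directly before the reporting rule introduces the scale: the Sponsor-Investigator "assesses the severity of each adverse event as mild, moderate, or severe". The reporting rule then uses the top grade of that scale, twice, and introduces no other classification. The natural reading is that the trigger is the top intensity grade.

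**Step 2: apply the rule literally.** Take related events only; by section 2.20 these are the possibly, probably or definitely related ones. Cross the three intensity grades with two levels of seriousness, which gives 3 × 2 = 6 kinds of related event.

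| Intensity | Serious outcome | Reported under section 2.20 as printed | Reported if seriousness were the trigger |
|---|---|---|---|
| Mild | No | No | No |
| Mild | Yes | **No** | **Yes** |
| Moderate | No | No | No |
| Moderate | Yes | **No** | **Yes** |
| Severe | No | **Yes** | **No** |
| Severe | Yes | Yes | Yes |

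The two triggers disagree in three of the six kinds. In two, a related event with a serious outcome has no stated reporting duty. In one, a non-serious event is reported because it was intense. This counts categories; it says nothing about how often each occurs.

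**Step 3: look for another route.**

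- Section 2.3 applies before enrolment and concerns disease history.
- Section 2.18 removes a participant with a newly diagnosed serious disease from the study, but imposes no report.
- Section 2.21 (Amendments) requires reports to the Ethics Committee of emergency deviations from the protocol, not of adverse events.
- Section 2.22 (Monitoring) gives monitors, auditors and inspectors access to records, but sets no reporting duty or deadline for events.
- Table 1 schedules safety at screening and at both visits, without saying what is recorded.

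None of these supplies a second adverse-event reporting route.

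**The case against.** The strongest case on the other side has three parts.

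**Condensation.** This is a journal article, and the full protocol approved by the ethics committee is not shown. Seriousness criteria and the layout of the adverse event form are details that an article commonly leaves to that document. This stands in part. A reader might infer that the trial never assesses seriousness, but the article cannot show that, because neither the full protocol nor the case report form is available. It does not excuse the trigger itself: the article prints a complete rule, with assessor, scale, condition, recipient, system and deadline, and the condition in it is the intensity grade.

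**A slip of wording.** The phrase may stand for serious adverse event; a relatedness condition and a 15-day limit to an ethics committee would fit that. The documents cannot settle it. The position right after the scale favours the literal reading, and if it is a slip, the published rule still misstates the duty.

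**No contradiction with the cited guideline is shown.** A reader might infer that section 2.20 departs from ICH E2A. In the article that citation is attached to the classification of relatedness only, and the guideline is not at hand. The point therefore rests on the article's own wording.

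Two further inferences are also unsupported. One is that the article's minimal-risk statement depends on the wrong classification. Section 2.16 (Risks) rests it on trained staff, certified instructors and a programme designed for postmenopausal women, and the Discussion rests it on a noninvasive intervention and free withdrawal; neither uses event grading. The other is that the share of home-based sessions measures the size of the gap. It does not, because it says nothing about how many events are serious yet graded below severe.

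**Conclusion.** The point holds as a defect in the rule as printed: reporting to the Ethics Committee is attached to intensity, so a related event with a serious outcome graded mild or moderate has no stated reporting duty in this article. The statement that such an event need not be reported applies to this wording only. It is not a finding that events have been or will be missed.

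The size cannot be given, since the article states no rate of adverse events by grade or outcome. The article describes the risk as minimal, so few events are likely to be affected. The primary endpoint, the power calculation and the planned Mann–Whitney test are unaffected. The point should be addressed because it concerns participant safety and is cheap to correct.

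The conclusion assumes that the trigger word carries the meaning of the scale it follows, and that the full protocol does not already state a separate seriousness rule. If the full protocol does, only the article's wording needs correcting.

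**What to change.** Reconcile section 2.20 with the full protocol, and then:

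1. State intensity (mild, moderate, severe) and seriousness as two separate classifications of each adverse event.
2. Make the trigger for the Ethics Committee report a serious adverse event that is possibly, probably or definitely related to the intervention. The existing definition of relatedness and the 15-day limit stay as they are.

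If the sponsor also wants severe but non-serious related events to go on being reported, the text should say so as a separate condition.

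The cost is a sentence or two in section 2.20. If seriousness is not already recorded, one field is added to the case report form. Nothing changes in the sample size or the primary analysis.

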### Amendments

2.21

Substantial amendments to the study design, organization, protocol, or relevant study documents must be submitted to the Ethics Committee for approval prior to implementation.

In emergencies, the investigator may deviate from the protocol without prior approval to protect the rights, safety, and well-being of participants. The study staff documents and reports any of these deviations to the Ethics Committee as soon as possible. Substantial amendments affect the safety, health, rights, or obligations of participants, impact the study objectives or the central research question, or involve a change of study site, principal investigator, or sponsor (ClinO, Art. 29) (21).

### Monitoring

2.22

To ensure accurate, complete, and reliable data, the study site and procedures may be reviewed by independent monitors. Participants’ data privacy is strictly maintained. All study records and source documents are also available to auditors and inspectors, including the Ethics Committee, with queries addressed by the investigator or designated staff.

